**Methods:**

This open-label, nonrandomized assessment compares the relative effectiveness of a combination prevention intervention with and without daily oral emtricitabine and tenofovir disoproxil fumarate (Truvada) PrEP with SMS-based adherence support. HIV-uninfected young MSM and TGW aged 18 to 26 years in Bangkok and Pattaya who self-report selling/exchanging sex at least once in the previous 12 months are recruited by convenience sampling and peer referral and are eligible regardless of their intent to initiate PrEP. At baseline, participants complete a standard assessment for PrEP eligibility and may initiate PrEP then or at any time during study participation. All participants complete a survey and HIV testing at baseline and every 3 months. Participants who initiate PrEP complete monthly pill pickups and may opt-in to SMS reminders. All participants are sent brief weekly SMS surveys to assess behavior with additional adherence questions for those who initiated PrEP. Adherence is defined as use of 4 or more pills within the last 7 days. The analytic plan uses a person-time approach to assess HIV incidence, comparing participant time on oral PrEP to participant time off oral PrEP for 12 to 24 months of follow-up, using a propensity score to control for confounders. Enrollment is based on the goal of observing 620 person-years (PY) on PrEP and 620 PY off PrEP.

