### Sample Size Calculation

This study focuses on the primary endpoint of incident HIV infection during follow-up, comparing person-time on PrEP and off PrEP. Participant uptake of PrEP, level of PrEP adherence, and cessation of PrEP use serve as secondary endpoints in this study.

As prospectively measured in the Bangkok MSM Cohort Study cohort [37], we expect that the participants will be a mixture of very high-risk MSM and TGW 18 to 24 years of age with an HIV incidence rate of 11 per 100 PY and high-risk MSM 22 to 26 years of age with an incidence rate of 5 per 100 PY. Assuming a 50/50 mixture, we expect an incident rate of 8.5 per 100 PY (range=7-10). On the basis of recent iPrEx open-label extension (iPrEx OLE) study, we assume a 50% reduction in incidence for the PrEP group versus off-PrEP group [38]. On the basis of empirical evidence, we expect that some 50% of the participants will choose to take PrEP.

The sample size of this study is 1240 participants based on the following assumptions: incidence without PrEP is 8.5 per 100 PY, a PrEP efficacy of 50%, time-on-PrEP of 50%, attrition of approximately 2% per month, power=0.8, α (one-sided)=.025, and inflation of the standard error of the hazard ratio by 0% to 20% after adjusting for confounding. From this assumption, we expect that a combined sample of 1240 (620 on PrEP and 620 not on PrEP) will be sufficient.

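### 620 + 620 person-years give 80% power only up to about 4% to 10% inflation of the standard error; at the 20% end of the stated range power is about 68% to 73%

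*Protocol article*

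**What the plan says.** The Sample Size Calculation section of the Protocol article sets out its inputs in one sentence. The off-PrEP rate is taken as 8.5 infections per 100 person-years, PrEP is taken to halve it, and half of the follow-up time is taken to be on the drug. Dropout is put at about 2% each month. The error rates are given as "power=0.8, α (one-sided)=.025". The last input is the allowance for the adjusted analysis: "inflation of the standard error of the hazard ratio by 0% to 20% after adjusting for confounding". The section gives the size as 1240 participants and concludes: "we expect that a combined sample of 1240 (620 on PrEP and 620 not on PrEP) will be sufficient". It names no formula and does not say at which point of the inflation range the figure was computed. It also gives a range of 7 to 10 per 100 person-years for the incidence.

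The Methods paragraph of the abstract uses the same two numbers in another unit: "Enrollment is based on the goal of observing 620 person-years (PY) on PrEP and 620 PY off PrEP".

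The Data Analysis section plans Wald tests for both versions of the primary analysis: a Poisson regression adjusted for baseline covariates, and a weighted pooled logistic model (marginal structural model) that also handles time-varying confounding.

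**The concern.** A single power of 0.8 stands beside a range of inflation, with no qualification. The natural reading is that 620 + 620 gives 80% power wherever in the range the inflation falls. A 20% larger standard error needs 1.2 squared, or 1.44 times, the information, so one size cannot give about 80% power at both ends.

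The difference matters for the analysis the trial most depends on. Participants choose whether to take PrEP, so the weighted model carries the causal claim, and weighting is where a larger standard error is most to be expected. If that analysis came out non-significant, it would be judged against a power that the design may not have had.

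**Working it through.** **Inputs, all from the Sample Size Calculation section unless noted.** Off-PrEP rate 0.085 per person-year (PY); hazard ratio 0.5, so on-PrEP rate 0.0425; equal time on and off PrEP; one-sided 0.025 (z = 1.960); power 0.80 (z = 0.842, sum 2.802). The unit, 620 PY in each state, is from the abstract. Let f be the factor by which the standard error (SE) is inflated.

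**Step 1: reproduce 1240.** Schoenfeld's formula gives events = 4 × 2.802² × f² / (ln 0.5)² = 65.3 × f². The mean rate is (0.085 + 0.0425)/2 = 0.06375 per PY, so total PY = 65.3 × f² / 0.06375 = 1025 × f².

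- f = 1.00: 1025 PY
- f = 1.10: 1240 PY
- f = 1.20: 1476 PY

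The stated 1240 is met at 10% inflation, the midpoint of the range. This is an inference, since the article names no formula.

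**Step 2: power at 620 + 620 PY.** Expected infections are 620 × 0.085 = 52.7 off PrEP and 620 × 0.0425 = 26.35 on PrEP, 79.05 in total.

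- Wald, log rate ratio: SE = √(1/52.7 + 1/26.35) = 0.2386; Z = 0.6931/0.2386 = 2.905.
- Schoenfeld: Z = 0.6931 × √(79.05/4) = 3.081.

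Power = Φ(Z/f − 1.960):

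| SE inflation | Wald | Schoenfeld |
|---|---|---|
| 0% | 82.8% | 86.9% |
| 10% | 75.2% | 80.0% |
| 20% | 67.8% | 72.8% |

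The largest inflation that keeps 80% is Z/2.802 − 1: 3.7% (Wald) and 10.0% (Schoenfeld). Freedman and rate-difference formulas (69.5% at 20%, limit 5.8%) and a square-root transform (70.7%, limit 7.3%) fall in between. A simulation of one million pairs of Poisson counts gave 84.7% for the unadjusted Wald test, inside the 0% row.

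**Step 3: the plan's own incidence range, at 20% inflation.** At 7 per 100 PY, power is 59.4% (Wald) to 64.4% (Schoenfeld). At 10 per 100 PY it is 74.7% to 79.5%. None of the formulas tried reaches 80% at 20% inflation anywhere in the range.

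**Step 4: what 20% inflation would need.** Wald: PY per state = (1/0.085 + 1/0.0425) × (1.2 × 2.802/0.6931)² = 830, or about 1660 in total. Schoenfeld: 1476 in total (step 1). In infections, PY × 0.06375 gives:

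| SE inflation | Schoenfeld | Wald |
|---|---|---|
| 0% | 65 | 74 |
| 10% | 79 | 89 |
| 20% | 94 | 106 |

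At 620 + 620 PY and 20% inflation, the hazard ratio detectable with 80% power solves |ln HR| = 1.2 × 2.802 × SE, with the on-PrEP events recomputed for that ratio. It is about 0.43 (Wald) to 0.47 (Schoenfeld).

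**Step 5: the participant reading.** With 2% lost per month, m months of follow-up give PY = 1240 × 0.99 × (1 − 0.98^m)/0.02/12, counting half of each month's loss within that month. Time is split equally on and off PrEP.

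| Follow-up | Total PY | Power at 20% inflation (Wald to Schoenfeld) |
|---|---|---|
| 12 months | 1101 | 63% to 68% |
| 18 months | 1559 | 77% to 82% |
| 24 months | 1965 | 86% to 90% |

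**The case against.** The strongest reply is that the allowance was built in. Schoenfeld at 10% inflation gives 1240 almost exactly, and a midpoint is a legitimate planning value. This stands, and it rules out a stronger reading that a reader might infer, namely that the inflation was listed and then ignored. What remains is that the article presents the whole range under one power figure and does not say that a midpoint was used.

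A reader might also take 68% power and a 4% limit as the answer. Those are the Wald results alone. They suit the planned Wald tests, but the formula that reproduces the plan's own size gives 73% and 10%, so the documents support only a range.

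Thirdly, the sample size section says participants and lists attrition, and follow-up may run to 24 months. On that reading the shortfall can disappear, so the documents do not support saying that the trial is underpowered however it is run. However, the standard follow-up is 12 months. The second year is optional and, according to the Recruitment and Consent section, depends on the study's timetable.

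Finally, if the 20% were an inflation of the variance, f would be √1.2 = 1.095. Schoenfeld would then need 1230 PY, and 1240 would cover the whole range by that formula (80.3%), though not by Wald (75.6%). The text says standard error, so this does not answer the point. It is one more reason to state the calculation.

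**Conclusion.** The point holds in a bounded form. Taken as person-years, 620 + 620 does not give the stated 80% power over the upper part of the stated inflation range under any formula tried. The shortfall at the 20% end is about 7 to 12 percentage points. It is larger if incidence is at the low end of the plan's range, and nearly gone by Schoenfeld (79.5%) at the high end. The conclusion assumes the abstract's unit, equal time on and off PrEP, the stated rates, and inflation applied to the standard error as written. On the participant reading, it holds for 12 months of follow-up, depends on the formula at 18 months, and does not hold if everyone is followed for 24 months. That the allowance was set at 10% is a reconstruction, not something the article states.

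**What to change.** In the abstract and the Sample Size Calculation section:

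1. Reconcile participants with person-years. If 1240 is a number of participants, state the follow-up assumed.
2. Name the formula, and the inflation value at which 1240 gives 80% power.
3. If the person-year goal stands, restate power as about 83% to 87% at 0%, 75% to 80% at 10% and 68% to 73% at 20% inflation, with a detectable hazard ratio at 20% of about 0.43 to 0.47. Once the formula is named, each range becomes a single figure.
4. Give the target for the adjusted analysis as infections: about 65 to 74 at 0%, 79 to 89 at 10% and 94 to 106 at 20% inflation. The extra follow-up already allowed can then be judged against the right number.

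This changes wording only and adds no procedure. The price is a less favourable stated power.

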### Data Analysis

Each week of study participation at risk for HIV for each participant falls into 1 of 4 mutually exclusive categories of person-time: (1) on PrEP, good adherence; (2) on PrEP, poor adherence; (3) off PrEP, recent PrEP discontinuation (in last 30 days); and (4) off PrEP, no recent PrEP exposure. Individuals are considered at risk for HIV until the first positive HIV test result or until the last HIV negative test result in the case of administrative censoring, loss-to-follow-up, or another censoring event.

The primary outcome analysis will compare HIV incidence during person-time on PrEP (categories 1 or 2) to HIV incidence during person-time not on PrEP (categories 3 or 4), with a simplified analysis following the analytic methods used by other PrEP open-label studies, and a more complex analysis using marginal structural models to account for time-varying confounding. Secondary outcome analyses will explore whether HIV incidence differs between participants on PrEP with good versus poor adherence (category 1 vs category 2) and whether HIV incidence differs between participants not on PrEP who have recently discontinued PrEP use versus who do not have recent PrEP exposure (category 3 vs category 4).

A more complex primary outcome analysis will be conducted using marginal structural models, following the methods proposed by Robins et al [39] As participants self-select into the PrEP group, the difference in incidence between those on PrEP and not on PrEP may be biased due to confounding. Propensity score methods will be used for bias reduction for the estimation of the causal effect of being on PrEP on HIV incidence, an approach that is well documented in nonrandomized pharmacoepidemiologic studies [40]. This will be an as-treated analysis that will account for discontinuation of PrEP, and as PrEP initiation and cessation may occur over the course of follow-up, and participants may cease and restart sex work, potential confounders may be time-varying, further complicating the estimation of causal effects.

In marginal structural models, inverse probability of treatment and censoring weights (IPTCWs) will be used in weighted, pooled logistic regression models of HIV infection. The data for each participant are structured such that each record represents 1 person-week of time either on PrEP or not on PrEP [39]. The odds ratio from the weighted, pooled regression provides an estimate of the hazard ratio for HIV infection associated with PrEP initiation similar to Cox time-dependent regression [41,42]. The IPTCWs at time *t_i_* incorporate the estimated probability of the observed treatment history and the estimated probability of prior censoring. Creating the IPTCWs requires estimating inverse probability of treatment weights (IPTWs), inverse probability of censoring weights (IPCWs), and stabilization weights.

To estimate the IPTWs, a series of logistic regression models will be used to estimate the propensity of transition from one treatment state at time *t_i-1_* to a new treatment state at time *t_i_*. These analyses will be limited to participants who were HIV-negative at time *t_i_*, and the analyses will include time-invariant (ie, baseline) covariates, and time-varying covariates from time *t_i_* or earlier. Potential confounders to be included in the propensity score models of treatment status will be identified based on existing knowledge and based on exploratory analyses. Factors associated with PrEP acceptability among Thai young MSM and TGW include STI history, frequency of anal intercourse, HIV testing history, PrEP awareness, and insurance status [13], and factors associated with PrEP acceptability in other populations include perceived risk for HIV, use of condoms, sexual identity, education, concerns about PrEP use, and sex with casual or exchange partners [43]. Based on the estimated coefficients, the predicted probability of the observed treatment will be estimated, and this estimate will be inverted to give the inverse probability of the observed treatment at time *t_i_*, given the observed treatment at time *t_i-1_*. Prior treatment history will be incorporated by multiplying the predicted probability of treatment by the probabilities of not receiving the observed treatment at each of the previous time points.

Stabilization weights will be similarly estimated, but, in contrast, they will be based on logistic regression models including only time-invariant covariates. The IPTWs will be multiplied by the stabilization weights to improve their performance. The IPCWs will be similarly estimated and stabilized, but using transition from observed to unobserved in place of transition between PrEP use and nonuse, and the covariates used for the censoring model may differ from the covariates used in the treatment model. Finally, the product of the stabilized IPTWs and the stabilized IPCWs will provide the IPTCWs that will be used in the pooled logistic regression model to estimate the hazard ratio of HIV infection during time on PrEP and time off PrEP. The pooled logistic regression will include all time-invariant covariates used to create the stabilization weights and additional time-invariant covariates may be identified through exploratory data analysis.

The estimated log-odds of HIV infection and the standard error of the estimate from the pooled logistic will be used to evaluate whether the hazard of HIV differs between time on PrEP and time off PrEP, with the null and alternative hypotheses evaluated using the Wald statistic.

H10: The hazard of HIV during time on PrEP will not differ from the hazard of HIV for time not on PrEP: HIV hazard ratio=1.

H1a: The hazard of HIV during time on PrEP will differ from the hazard of HIV for time not on PrEP: HIV hazard ratio1.

The simplified primary outcome analysis will be conducted using Poisson regression, following the methods used by Grant et al [38]. The simplified analysis will have the benefit of easier interpretation but lack the ability to control for time-varying confounders that may be both causes and consequences of PrEP use (eg, sexual risk behavior and risk compensation).

The Poisson regression model will control for baseline covariates and include a time-varying indicator for PrEP status. The outcome will be assessed using a person-time approach, assessing HIV incidence densities among young MSM and TGW on and off daily oral PrEP over follow-up. In the Poisson regression, the Wald statistic will be used to evaluate the coefficient for PrEP status to distinguish between the null and alternate hypotheses.

H10: The HIV incident rate during time on PrEP will not differ from the incident rate for time not on PrEP: HIV incident rate ratio=1.

H1a: The HIV incident rate during time on PrEP will differ from the incident rate for time not on PrEP: HIV incident rate ratio 1.

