### Intervention Effectiveness Study Design

The study is an open label, nonrandomized assessment comparing the relative effectiveness of a combination preventive intervention with and without daily oral tenofovir/emtricitabine (FTC; Truvada) PrEP with adherence support. We follow those young MSM and TGW who choose to initiate PrEP as part of the combination package, and those who agree to participate but do not choose to start on PrEP, for whom all other intervention components will be offered. The outcome will be assessed using a person-time approach, assessing HIV incidence densities among young MSM and TGW on and off daily oral PrEP over 12 to 24 months of follow-up. Participants are enrolled for a standard follow-up period of 12 months; however, given the importance of remaining on PrEP for people in high-risk contexts, we offer the option to re-enroll for an additional 12 months. All participants, regardless of PrEP status complete quarterly study visits and weekly, brief behavioral SMS surveys. Participants who initiate PrEP are required to attend monthly medication pickup visits. Figure 1 displays the flow diagram of the study with a brief description of study visit activities.

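### Two models are each called the primary outcome analysis, with one alpha and no statement of which model decides

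*Protocol article*

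**What the plan says.** Protocol article, Data Analysis: the primary outcome analysis compares incidence during time on PrEP with incidence during time off PrEP, "with a simplified analysis following the analytic methods used by other PrEP open-label studies, and a more complex analysis using marginal structural models". The marginal structural model is introduced as the more complex primary outcome analysis. It is a pooled logistic regression weighted for treatment and censoring, and it yields a hazard ratio. Later in the section: "The simplified primary outcome analysis will be conducted using Poisson regression". That model adjusts for baseline covariates, carries a time-varying PrEP indicator and yields an incidence rate ratio. The article says it will "lack the ability to control for time-varying confounders that may be both causes and consequences of PrEP use". Each model is followed by a null and an alternative hypothesis, labelled H10 and H1a both times, and each is tested with a Wald statistic.

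Protocol article, Sample Size Calculation: one set of operating characteristics is given, "power=0.8, α (one-sided)=.025, and inflation of the standard error of the hazard ratio by 0% to 20% after adjusting for confounding".

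Protocol article, Cost-Effectiveness Analysis: infections averted are to come from the primary outcomes analyses, in the plural.

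**The concern.** A primary analysis is named in advance so that one estimate and one test carry the main conclusion. Here two models hold that position. The text does not rank them, require both to succeed, divide alpha, or say what happens if they differ. Three things follow.

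- The investigators could report either result as primary after seeing both, and still be within the text.
- One of the two is the model that, by the article's own account, cannot deal with time-varying confounding. The article expects such confounding to be possible because participants choose PrEP and may start or stop both PrEP and sex work.
- The infections-averted figure, and the cost-effectiveness classification built on it, have no single defined source.

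This is not a detail left to an unseen analysis plan. The article itself gives primary status to two models, so a plan that named only one would depart from it.

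**Working it through.** **Inputs.** From Sample Size Calculation: "incidence without PrEP is 8.5 per 100 PY, a PrEP efficacy of 50%, time-on-PrEP of 50%, attrition of approximately 2% per month", with one-sided alpha 0.025 and power 0.80, so z = 1.960 and 0.842. From the Abstract (Methods): 620 person-years (PY) on and 620 PY off PrEP. From Intervention Effectiveness Study Design: 12 months of standard follow-up.

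**1. The plan's own figure is sized for one test.**
- On-PrEP rate: 0.085 × 0.5 = 0.0425 per PY. Mean rate: (0.085 + 0.0425)/2 = 0.06375 per PY.
- Freedman events: (1.960 + 0.842)² × (1.5/0.5)² = 70.6. PY: 70.6/0.06375 = 1108. Mean 12-month retention at 2% loss per month: (1 − 0.98¹²)/(−12 ln 0.98) = 0.888. Participants: 1108/0.888 = 1248, against 1240 stated.
- Schoenfeld events: 4 × (1.960 + 0.842)²/(ln 2)² = 65.3. With 10% inflation of the standard error: 65.3 × 1.21/0.06375 = 1240 PY, which equals the person-time goal.

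Both routes use a single test at one-sided 0.025. No allowance for a second test is needed to reach 1240.

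**2. Error rate if either test may carry the claim.** With two Wald statistics of correlation ρ, each valid at 0.025, the chance of at least one false positive is 0.05 − P(both Z > 1.96). The document gives no ρ, so it is assumed.

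| ρ | one-sided error |
|---|---|
| 0.99 | 0.028 |
| 0.95 | 0.032 |
| 0.9 | 0.035 |
| 0.8 | 0.039 |
| 0.7 | 0.042 |
| 0 | 0.049 |

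The ceiling for any correlation is 0.025 + 0.025 = 0.05. Both tests use the same people, infections and contrast, so the upper rows of the table are the more plausible ones. If one model decides, or both must succeed, the rate stays at or below 0.025.

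**3. Sensitivity of a Poisson test to residual confounding.** Assume no true effect and a spurious rate ratio b. Events are 620 × 0.085 = 52.7 off PrEP and 52.7b on PrEP. SE = √(1/52.7 + 1/(52.7b)), and the chance of wrongly declaring benefit is Φ(−ln b/SE − 1.96).
- b = 0.95: 0.045
- b = 0.90: SE 0.200, 0.105/0.200 = 0.526, giving 0.076
- b = 0.80: SE 0.207, 0.223/0.207 = 1.080, giving 0.19
- b = 1/0.90 = 1.11: SE 0.190, giving 0.006

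The last line shows that bias in the other direction makes a false claim less likely. The values of b are illustrations, not estimates.

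**4. Cost of keeping both as primary with either sufficient.** Bonferroni at 0.0125 each needs 80 Schoenfeld events in place of 66. With 52.7 and 26.35 expected events at 620/620 PY, the Wald standard error is √(1/52.7 + 1/26.35) = 0.239. Power falls from 0.83 to 0.75 with no inflation of the standard error, and from 0.68 to 0.57 with 20% inflation.

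**The case against.** The best case on the other side is that the plan does lean one way. The Abstract mentions only the propensity score approach. The sample size is stated on the hazard ratio with its standard error inflated after adjusting for confounding, and the hazard ratio is the weighted model's parameter. The Poisson model is called simplified, is valued for easier interpretation and has its limitation stated. Both models carry the same hypothesis labels, so they can be read as one hypothesis assessed in two ways. All of this stands, and it supports the choice of model in the fix. It does not remove the primary label from the Poisson model.

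Three stronger readings are tempting and are not supported.

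- A reader might infer that the 0.025 is already lost. It is lost only if either test may win, and the article does not say so. It only fails to exclude it.
- A reader might infer that the article concedes a biased Poisson result. It states that the model cannot control time-varying confounders. That is a limitation, and the model does adjust for baseline covariates.
- A reader might infer that the models will probably disagree. Nothing shows this. At the interim, off-PrEP time was 33 of 168 PY (20%), and 115 of 445 participants (26%) had not started at baseline. That is compatible with off-PrEP time coming mainly from people who never started, although the article does not split it.

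It is also fair to say that naming the weighted model does not settle everything. Some of its covariates may be chosen by exploratory analysis, and its weights may be unstable when off-PrEP time is scarce.

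**Conclusion.** The point holds as a double designation in the text: two primary models, two Wald tests, one alpha and no deciding rule. The main consequence is that the estimate carrying the primary conclusion and the infections-averted input is not fixed in advance. The error-rate consequence is conditional and modest: about 2.8% to 4.2% in place of 2.5% for assumed correlations of 0.99 to 0.7, never above 5%, and only if either test may count. That calculation treats both tests as valid under the null, so it does not measure confounding. What confounding would do to the Poisson result cannot be read from the document in size or direction. The alternatives are worded as a difference without direction, which changes nothing: two-sided 0.05 puts 0.025 in the direction of benefit. This should be corrected, but it does not undermine the design.

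**What to change.** Name the IPTCW marginal structural model as the single primary analysis, both for the hypothesis test at one-sided 0.025 and for the infections-averted input. Relabel the Poisson regression as supportive, reported with its rate ratio and interval and with no separate claim of success. Put the infections-averted source in the singular in Cost-Effectiveness Analysis.

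The change is one of wording. It needs no new data and leaves the planned 1240 as it is. What is given up is the simpler model as a route to a primary claim. The trial would then rest on a weighted estimate that may be less precise if off-PrEP time remains near the interim 20%. Requiring both models to succeed would also hold the error rate, but would still leave open which estimate feeds the cost-effectiveness analysis.

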### Combination Prevention Intervention

As of February 2019, 445 participants (417 MSM and 28 TGW) have contributed approximately 168 PY with 95% (73/77) retention at 12 months. 74.2% (330/445) of enrolled participants initiated PrEP at baseline, contributing to 134 PY of PrEP adherence based on a measure of 4 or more pills within the last 7 days, 1 PY nonadherence, and 33 PY PrEP nonuse/noninitiation. Monitoring of unexpected events has identified 7 social harms, predominantly related to unintentional participant disclosure of PrEP use and peer stigmatization of PrEP and HIV.

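### Category 4 pools people with no PrEP use to date and people who stopped more than 30 days ago, so the secondary category 3 versus 4 comparison cannot separate recency of stopping from self-selection into PrEP

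*Protocol article*

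**What the plan says.** The Data Analysis section assigns each at-risk person-week to one of four categories. The two off-PrEP categories are category 3, "off PrEP, recent PrEP discontinuation (in last 30 days", and category 4, "off PrEP, no recent PrEP exposure". Of the further comparisons it says: "Secondary outcome analyses will explore whether HIV incidence differs". The one at issue here asks "whether HIV incidence differs between participants not on PrEP who have recently discontinued PrEP use versus who do not have recent PrEP exposure".

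Under Study Visits, people who never start PrEP and people who stop it both remain in quarterly follow-up, so both supply off-PrEP weeks.

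The Data Analysis section also warns that, because participants choose PrEP for themselves, "the difference in incidence between those on PrEP and not on PrEP may be biased due to confounding". It describes the inverse-probability weights and the PrEP-status term of the Poisson model for time on versus time off PrEP. It does not say how category 3 versus 4 is to be adjusted.

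The Results report that "74.2% (330/445) of enrolled participants initiated PrEP at baseline" and give off-PrEP time as a single figure: "1 PY nonadherence, and 33 PY PrEP nonuse/noninitiation".

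**The concern.** A comparison of recent stoppers with other off-PrEP time invites a reading about risk just after stopping. For that reading, the two sides should differ in time since stopping and otherwise be alike. Here they also differ in whether the person ever took PrEP. The factors that the article links to PrEP acceptability (STI history, frequency of anal intercourse, perceived risk, condom use, casual or exchange partners) are plausibly linked to HIV risk as well. A higher or lower rate in category 3 could therefore appear when recency has no effect, and a real recency effect could be hidden.

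**Working it through.** The article states no figure for category 3 versus 4. Its total of 1240 (620 on and 620 off PrEP) belongs to the primary contrast and does not bear on this point.

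**Step 1: who can be in each category.**

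| Off-PrEP person-week | Category | PrEP used earlier in the study? |
|---|---|---|
| Stopped within 30 days | 3 | Yes |
| Stopped more than 30 days ago | 4 | Yes |
| Will start later | 4 | No |
| Never starts | 4 | No |

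The last two rows have no counterpart in category 3.

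**Step 2: size of the distortion.** Let *w* be the share of category 4 person-time from people with no PrEP use to date. Let *r* be their HIV rate divided by the off-PrEP rate of former users. If recency has no effect, the category 3 versus 4 rate ratio is 1/(*w r* + 1 − *w*). The article gives neither *w* nor *r*, so both are assumed.

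| *w* | *r* = 0.5 | *r* = 0.7 | *r* = 1.4 | *r* = 2 |
|---|---|---|---|---|
| 50% | 1.33 | 1.18 | 0.83 | 0.67 |
| 90% | 1.82 | 1.37 | 0.74 | 0.53 |
| 100% | 2.00 | 1.43 | 0.71 | 0.50 |

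For example, at *w* = 50% and *r* = 0.7 the ratio is 1/(0.35 + 0.5) = 1.18.

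**Step 3: what the article allows for *w*.**

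- Planning inputs (Sample Size Calculation): 50% choose PrEP and 50% of time is on PrEP. Non-choosers could then fill all off-PrEP time, so *w* could reach 100%.
- Interim data (Results): mean follow-up is 168/445 = 0.378 PY. The 445 − 330 = 115 baseline non-starters would supply 115 × 0.378 = 43 PY, more than the 33 PY off PrEP. Baseline starters would supply 330 × 0.378 = 125 PY, less than the 134 + 1 = 135 PY on PrEP. So either follow-up was not equal, or baseline non-starters spent at least 10 PY on PrEP. Under equal follow-up, each PY that baseline starters spent off PrEP needs one more on-PrEP PY from later starters. The split of the 33 PY is not identified.
- Assumed stopping rates: monthly stopping probability *h*, no restart, one year of follow-up without attrition, 1240 people, all starts at baseline. With λ = −12 ln(1 − *h*), off-PrEP time per starter is 1 − (1 − e^(−λ))/λ. Category 3 takes at most 30/365.25 = 0.082 PY per stop, and the rest is former-user time in category 4 (4a). Infections are at 8.5 per 100 PY.

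| Uptake | *h* | Category 3 PY (infections) | 4a PY | *w* |
|---|---|---|---|---|
| 50% | 2% | 10.6 (0.9) | 59 | 91% |
| 50% | 5% | 22.7 (1.9) | 134 | 82% |
| 50% | 10% | 35.8 (3.0) | 232 | 73% |
| 74.2% | 2% | 15.7 (1.3) | 87 | 79% |
| 74.2% | 5% | 33.7 (2.9) | 199 | 62% |
| 74.2% | 10% | 53.1 (4.5) | 345 | 48% |

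**Step 4: what a split costs in precision.** The standard error of the log rate ratio is about √(1/d₃ + 1/d_ref), where d is the number of infections.

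- Last row: d₃ = 4.5, and 4a has 345 × 0.085 = 29.3. The SE is 0.51, a 95% interval of about 2.7-fold either way. Pooled category 4 (345 + 320 = 665 PY, 56.5 infections) gives about 2.6-fold.
- First row: d₃ = 0.9, and 4a has 5.0. The SE is 1.15, about 9.5-fold. Pooled (59 + 620 = 679 PY, 57.7 infections) it is about 8-fold.

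The interval is wide mainly because category 3 is small, with or without the split.

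**The case against.** The plan only explores an incidence difference and claims no causal effect of stopping. A reader might infer that the comparison measures who chooses PrEP instead of the effect of recent stopping. The documents do not support that: the contrast mixes the two in unknown proportion, and some category 4 time comes from people who later choose PrEP.

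A reader might also infer that category 4 is nearly all never-user time. The 33 PY is not split by earlier use, the pro rata figure of 43 PY does not fit its own assumption, and follow-up so far is short. The stopping rule under Study Visits may also move poorly adherent time off PrEP. This objection stands.

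Adjustment of a secondary comparison may be specified in the full protocol or SAP, which are not shown, so its absence from the article is no fault. That stands too, but it does not settle the point. Adjusting for measured covariates leaves unmeasured differences between users and non-users, and a term for earlier PrEP use would amount to the split proposed here.

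The strongest objection is to the remedy. If few people stop, 4a is nearly empty and 3 versus 4b is almost the planned contrast. Quarterly HIV testing also places infections poorly within a 30-day window. Both stand as limits on what any version can show. Neither makes the pooled reference group suitable for a statement about recency.

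**Conclusion.** By its own definitions, the planned category 3 versus 4 comparison cannot isolate recency of stopping, because category 3 holds former users only and category 4 does not. The direction of the distortion is unknown. With *r* assumed at 0.7 or 1.4, the ratio with no recency effect is 1.18 or 0.83 at *w* = 50% and 1.43 or 0.71 at *w* = 100%. The assumed stopping scenarios put *w* between 48% and 91%, but the article reports no value.

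The point is limited to one exploratory secondary comparison. It should not be extended to the secondary endpoint of PrEP cessation, which is a behaviour that this contrast does not estimate. Nor does it touch the primary contrast (categories 1 and 2 versus 3 and 4), where the division of off-PrEP time plays no part.

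**What to change.** Split category 4 into 4a (former users, more than 30 days since stopping) and 4b (no PrEP use to date), and state whether PrEP use before enrolment counts. Report 3 versus 4a and 3 versus 4b separately, with person-years and infections in each. Read only 3 versus 4a as bearing on recency. Label any pooled 3 versus 4 result descriptive.

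The cost is a recoding of person-weeks already classified, with no new data; the survey already asks about PrEP use history. The downside is precision: 3 versus 4a will rest on few infections (about 1 to 5 in category 3 in the scenarios above) and may be uninformative. The report should say so, and should say that quarterly testing dates infections poorly against a 30-day window. The split removes the difference between former users and people without PrEP use, but not every confounder: people who restart quickly contribute to category 3 and not to 4a.
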